### Catchment and representativeness

The Montreal Children’s Hospital is one of two paediatric tertiary care centres in Québec and receives colorectal referrals from across the province, including from Nunavik and the Cree territory of James Bay, as well as selected complex referrals from other provinces. The registry therefore captures a substantial proportion, but not the entirety, of the incident paediatric HD and ARM population in Québec. To quantify representativeness rather than assert it, the age, sex, diagnosis and severity distribution of enrolled participants will be compared at each annual analysis against two external benchmarks: (i) expected provincial case counts, derived by applying published Canadian incidence estimates for HD (2.05 per 10,000 live births [1]) and ARM (approximately 1 in 2,162 births [3,4]) to Québec live-birth denominators; and (ii) the published case-mix of the ARM-Net and PCPLC registries [11,13]. Aggregate, non-identifying information on patients who are approached but decline enrollment (age band, diagnosis, and referral region) will also be recorded so that a non-participation comparison can be reported. Any material divergence, for example under-representation of remote communities or of the most severe Krickenbeck categories, will be reported explicitly alongside registry outputs and taken into account when interpreting external validity.

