### Eligibility criteria

Inclusion and Exclusion Criteria are described in Table 1.

**Table 1 pone.0356813.t001:** Inclusion and exclusion criteria.

Inclusion criteria	Exclusion criteria
Aged 0–17 years	Aged 18 years or older
Documented diagnosis of HD or ARM	No diagnosis of HD or ARM
Patients and/or their caregivers or authorised representatives must be able to provide informed consent	Unable to provide consent

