### Outcome measures

The primary outcome and its definition are described in detail below. Pre-specified secondary outcomes are presented in Table 2 below, each with its definition, instrument or data source, timing of ascertainment, and analytic role.

**Table 2 pone.0356813.t002:** Pre-specified primary and secondary outcomes.

Outcome	Definition	Instrument / Data Source	Timing of Ascertainment	Priority	Analytic Role
**Time to fecal continence**	First clinic visit (confirmed at subsequent visit) at which the participant meets social continence threshold: BCS criteria (ARM) or BFS ≥ 17 (HD), from date of definitive repair	BCS (ARM) [16] or BFS (HD) [17], parent/caregiver proxy to age 11; self-report from age 12	Annual visits from age 3	**PRIMARY**	Kaplan–Meier estimation; Cox proportional hazards regression; Fine-Gray model for competing risks; landmark analyses at ages 5 and 10
HD-associated enterocolitis (HAEC)	≥1 physician-confirmed episode meeting Ruttenstock criteria requiring medical treatment	Clinical record review; REDCap adverse event log	Each annual visit; first episode date recorded	Secondary 1	Cox regression / Fine-Gray competing risks; descriptive incidence rate
Reoperation rate	Any unplanned surgical return to the operating room following index repair	Operative report review; REDCap surgical procedure log	Cumulative from index repair; each annual visit	Secondary 2	Cox regression / Fine-Gray competing risks; cumulative incidence curve
Disease-specific quality of life	HAQL total score and subscale scores (age-appropriate version)	HAQL questionnaire, self- or proxy-report [18]	Ages 6, 10, and 14 years	Secondary 3	Linear mixed-effects model (repeated measures); descriptive means by group
Transition readiness	Transition Readiness Assessment Questionnaire	TRAQ [19], self-report	Ages 14 and 17 years	Secondary 4	Linear mixed-effects model; descriptive score trajectory
Loss to follow-up (LTFU)	No clinic encounter, survey, or successful contact for ≥18 months while under age 18 and not yet transitioned	REDCap contact log; clinic attendance record	Flagged at 18-month mark; reviewed at each annual analysis	Secondary 5	Logistic regression (ever-lost vs retained); descriptive LTFU rate

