**Objective 3:** Factors associated with key outcomes. Time to achievement of fecal continence will be estimated using the Kaplan–Meier method, with curves reported separately for ARM and HD given the use of disease-specific instruments. Given the embryological, surgical, and prognostic distinctions between the two conditions, and the use of disease-specific continence instruments, multivariable analyses will be conducted separately for ARM and HD rather than as a single combined model. For each disease cohort, a Cox proportional hazards model will be fitted with disease-appropriate pre-specified candidate predictors: for ARM, Krickenbeck category, age at index repair, sex, syndromic status, and area-level deprivation quintile; for HD, length of aganglionosis, age at index repair, sex, syndromic status, and area-level deprivation quintile. The proportional hazards assumption will be tested for each model using Schoenfeld residuals. Where competing risks are present (death or transition prior to the continence event), the Fine-Gray subdistribution hazard model will be applied within each cohort. Pre-specified landmark analyses will report the proportions achieving continence by age 5 and age 10 for each disease, to allow benchmarking against published ARM and HD cohort data. For each disease-specific model, multivariable Cox regression will be triggered only once the events-per-variable (EPV) threshold of 10 is met within that cohort at interim review; otherwise analyses for that cohort will be limited to descriptive and unadjusted comparisons.

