## Strengths and limitations

The principal strengths of the COCOE Registry are its prospective, longitudinal design with follow-up to age 18; its use of validated, age-stratified, disease-specific instruments administered in both official languages; its embedding within an established multidisciplinary clinical pathway rather than a parallel research process; and the pre-specification of outcomes, analyses, missing data handling, and adherence metrics before any analysis is conducted.

Several limitations follow directly from the design and should temper interpretation of registry outputs. The registry is single-centre. Although COCOE serves a wide provincial and inter-provincial catchment, its case-mix reflects a tertiary referral pathway and is likely to be enriched for complex, syndromic, and reoperative presentations relative to the population of all children born with HD or ARM in Canada. Families living at a distance from Montréal, families without stable housing or telephone contact, and families whose preferred language is neither French nor English are plausibly under-represented at both enrolment and follow-up; the resulting bias would favour better-resourced families with better measured outcomes, which is the direction that most threatens the validity of continence and quality-of-life estimates. Registry outputs should therefore be read as describing a referred paediatric colorectal population rather than as national incidence or outcome estimates, and comparisons with ARM-Net and PCPLC data should be made with case-mix in mind [11,13]. The registry infrastructure, data dictionary, and REDCap instruments have been deliberately designed to be transferable to additional Canadian centres, and multicentre expansion through CanCORPS is the primary planned mitigation.

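### Reoperation is counted from index repair in every enrolee, wherever repaired, so referral after a failed repair would bias its cumulative incidence upward

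*Protocol article*

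**What the plan says.** The reoperation row of Table 2 (Outcome measures) gives the event as "Any unplanned surgical return to the operating room following index repair", its ascertainment as "Cumulative from index repair; each annual visit", and its analysis as "Cox regression / Fine-Gray competing risks; cumulative incidence curve". The text under the table repeats the definition and ranks it as the second secondary outcome. Objective 1 of the Statistical analysis section names reoperation among the outcomes for Cox and Fine-Gray modelling and lists the candidate predictors: diagnosis type, severity category, age at index repair, sex, syndromic status and deprivation quintile.

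Table 1 (Eligibility criteria) asks for age 0–17, consent, and "Documented diagnosis of HD or ARM". It sets no condition on place of repair or previous reoperation.

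Two other sections describe who reaches the centre. Catchment and representativeness says that it receives colorectal referrals from across Québec "as well as selected complex referrals from other provinces". Strengths and limitations says that the case-mix "is likely to be enriched for complex, syndromic, and reoperative presentations" relative to all affected children in Canada.

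**The concern.** A cumulative incidence curve from index repair assumes that children are in the risk set for reasons unrelated to whether the repair later fails. A child repaired elsewhere and sent to COCOE for a redo breaks that assumption: the event, or its imminence, is the reason for entry. Children repaired elsewhere whose repair held have less reason to be referred, so the denominator holds fewer of them than it should. The plan neither separates these children from those repaired at COCOE nor brings them into the risk set only from enrolment.

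At stake are the second-ranked secondary outcome, its curve, and the regression on it. A reader would take the curve as the risk of reoperation after repair, when part of it could reflect the route into the registry. The planned representativeness checks compare age, sex, diagnosis and severity, and none of these would reveal the problem.

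**Working it through.** **Figures in the plan.** The protocol states no reoperation rate and no share of children referred for a redo, so there is no stated figure to reproduce for this outcome. Its enrolment figures do reproduce: (5 + 3) × 12 = 96 a year; 96 × 5 = 480; 480 + 200 = 680.

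**How many may enter after repair.** Re-engaged previous cases number 3 × 12 × 5 = 180 over five years, which is 180/480 = 37.5% of enrolees without the backlog. With the backlog of 150–200 added, the share is 330/630 = 52% to 380/680 = 56%. Many of these children would enter after index repair. They are not described as redo referrals, so this shows only that late entry is common.

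**Upper-bound illustration (both inputs assumed).** Let p be the true cumulative reoperation rate and f the share of enrolees who entered for a redo. If every such child counts as an event, observed rate = f + (1 − f) × p.

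| f | p = 10% | p = 20% |
|---|---|---|
| 5% | 0.05 + 0.95 × 0.10 = 14.5% | 0.05 + 0.95 × 0.20 = 24% |
| 10% | 0.10 + 0.90 × 0.10 = 19% | 0.10 + 0.90 × 0.20 = 28% |
| 20% | 0.20 + 0.80 × 0.10 = 28% | 0.20 + 0.80 × 0.20 = 36% |

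**Simulation (inputs also assumed).** The true 5-year risk was 20%, with 4,000 children repaired at the centre and 4,000 elsewhere. Outside-repaired children could be referred at a random time whatever their outcome, or immediately after a reoperation. The estimates are Kaplan–Meier 5-year risks.

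| Referred after a reoperation | Referred regardless of outcome | From index repair, all enrolees | Delayed entry at enrolment | Centre repairs only |
|---|---|---|---|---|
| 0% | 50% | 20.6% | 20.6% | 20.4% |
| 50% | 50% | 21.3% | 19.1% | 19.1% |
| 50% | 10% | 25.2% | 20.2% | 20.1% |
| 50% | 5% | 25.8% | 20.2% | 20.2% |

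Late entry alone does no harm. Bias appears when reoperation drives referral, and it grows as outcome-unrelated referral becomes rarer. Delayed entry removes it here because each triggering reoperation precedes entry. It would not do so for a child enrolled first and reoperated afterwards.

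**Regression.** The direction is open. If severe cases are referred whatever happens and mild ones only after failure, the mild group's rate is inflated and the severity effect shrinks. If failures in severe cases are referred more readily than failures in mild ones, the effect grows.

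**The case against.** The strongest reply is that the mechanism is inferred. The Sample size section names new cases, re-engaged cases and patients already followed at the centre; none is a redo-referral stream. Children repaired elsewhere can also arrive without a reoperation, since both diseases need lifelong follow-up, the centre is one of two tertiary paediatric centres in Québec, and 40–50% of participants are expected in bowel management at a given visit. The event must be unplanned, which may exclude a scheduled redo, and reoperations done elsewhere may be under-recorded. Either would offset some inflation. The limitations section discloses the enrichment and asks that outputs be read as describing referred patients. The choice of analysis set might be made in an analysis plan that is not shown.

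Most of this bears on size, and there it stands. It does not remove the point. The article itself fixes the origin and leaves the population unrestricted, and it concedes enrichment for the very event being counted. The caveat limits generalisation but does not restore the missing successes to the risk set. The only bias direction it spells out concerns better-off families with better results, which is a different matter.

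Stronger readings are tempting but unsupported. A reader might infer that successes repaired elsewhere never reach the centre, that a redo referral has the event almost by definition, or that severity and syndromic status will falsely emerge as risk factors. The documents establish none of these. A reader might also infer that the clocks conflict in the primary analysis, because continence runs "from date of definitive repair" while the ARM covariates are "Krickenbeck category, age at index repair, sex, syndromic status, and area-level deprivation quintile". That would need definitive repair to mean the redo, which the article nowhere says. Age at first repair can in any case be a legitimate baseline covariate under another origin.

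**Conclusion.** The point holds in conditional form. As written, entry to the cohort can depend on the reoperation outcome, and nothing in the plan corrects for it. To the extent that children repaired elsewhere enter because the repair failed, the cumulative incidence from index repair is biased upward; the coefficients may move either way. That the rate is inflated by any particular amount is not shown. The 14.5–36% range rests on an assumed true rate of 10–20% and an assumed redo-referral share of 5–20%, and is an upper bound for those inputs. The simulated 25–26% against a true 20% is likewise only an illustration. This is a worthwhile correction to a secondary outcome, and formal analyses have yet to be conducted, so it can still be pre-specified.

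**What to change.** 1. Derive two fields at entry: place of index repair, and reoperation status with referral reason. The assessment form already captures referral details and surgical history, and procedures are recorded with dates.
2. In Table 2 and Objective 1, make the main reoperation cumulative incidence and its Cox/Fine-Gray model an analysis of children whose index repair was done at COCOE.
3. Report children repaired elsewhere as a separate stratum, with delayed entry at enrolment and only later reoperations counted. Show referral reason within it, because delayed entry does not help where the redo follows enrolment.
4. State whether a redo scheduled after referral counts as unplanned.
5. Say whether the enrolment-date rule for prevalent cases in the Sample size section, written for continence, also applies to reoperation. If it does, it conflicts with the index-repair origin in Table 2.

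The cost is two derived fields and a few sentences. The real downside is fewer events in the main reoperation model, which may delay the point at which the threshold of 10 events per variable is met.

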## Introduction

Colorectal disorders, particularly Hirschsprung's disease (HD) and anorectal malformations (ARM), represent significant challenges in paediatric healthcare, with lifelong implications for affected children and their families [1–4]. HD is a congenital condition characterised by the absence of ganglion cells in the distal colon, leading to functional intestinal obstruction [1]. In Ontario, Canada, the incidence of HD has been estimated at 2.05 per 10,000 live births [1]. ARM, which encompasses a spectrum of congenital anomalies affecting the anorectal region and frequently associated organ systems, occurs at approximately 1 in 2,162 births in Alberta, with a notable male prevalence (1.7:1) [3,4]. Both conditions require early, often complex, surgical intervention and are associated with lifelong impacts on quality of life, growth, and development.

The management of paediatric colorectal disorders has advanced significantly with the development of specialised multidisciplinary centres, such as the Montreal Children's Hospital's Colorectal Centre of Excellence (COCOE).^8^ This centre is the first of its kind in Québec. Despite advances, children with these disorders often face ongoing challenges, including multiple surgeries, bowel management programmes, and psycho-social support needs. Long-term follow-up is critical, as many patients experience complications such as faecal incontinence, enterocolitis, and issues related to transition from paediatric to adult care [5–7]. For families, these challenges translate into substantial emotional and financial strain, particularly as patients age out of paediatric services [8–10].

Internationally, the importance of systematic data collection has been recognised through the establishment of prospective registries and research consortia. The European Anorectal Malformation Network (ARM-Net) [11,12] and the Paediatric Colorectal and Pelvic Learning Consortium (PCPLC) [13] are leading examples. The PCPLC registry has enabled robust, multicentre research: Rice-Townsend et al [14] found that only 24% of patients with ARM achieved full bowel control across over 500 patients, and Kastenberg et al. [15] demonstrated that rates of postoperative enterocolitis remain high regardless of surgical timing.

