The primary outcome is time to achievement of fecal continence from the date of definitive surgical repair, analysed as a time-to-event outcome. For participants with ARM, continence is assessed using the Baylor Continence Scale (BCS) [16], with social continence defined as no soiling episodes in the preceding 4 weeks per published BCS criteria, completed by the parent or caregiver proxy up to age 11 and by self-report from age 12. For participants with HD, continence is assessed using the Bowel Function Score (BFS) [17], with social continence defined as a BFS score ≥ 17, administered to the parent or caregiver proxy up to age 11 and by self-report from age 12. Both instruments are administered at every annual clinic visit beginning at age 3 years. The earliest clinically meaningful assessment for continence is age 3, consistent with normal developmental milestones for voluntary bowel control. Participants will be censored at age 18, death, transition to adult care, or loss to follow-up, whichever occurs first.

Pre-specified secondary outcomes, listed in priority order, are: (1) Hirschsprung-associated enterocolitis (HAEC), defined as at least one physician-confirmed episode meeting the Ruttenstock diagnostic criteria and requiring medical treatment, assessed at each annual visit [20]; (2) reoperation rate, defined as any unplanned surgical return to the operating room following index repair, assessed cumulatively; (3) disease-specific quality of life, measured using the HAQL [18] at ages 6, 10, and 14 years using age-appropriate versions; (4) transition readiness, assessed at ages 14 and 17 years using the validated Transition Readiness Assessment Questionnaire (TRAQ) [19], and (5) loss to follow-up rate, defined operationally in the Loss to Follow-Up section. Each secondary outcome will be reported descriptively and, where the events-per-variable threshold is met (see Sample Size section), included as an endpoint in pre-specified multivariable analyses with the analytic role specified in the Statistical Analysis section.

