### Patient-reported outcomes

During clinic visits or between encounters (online or paper), families are asked to complete validated surveys addressing multiple domains of well-being (Table 3). Surveys are available in English and French. Instruments include the Hirschsprung's and Anorectal Malformation Quality of Life (HAQL) questionnaire (disease-specific symptoms and quality of life, with age-specific and stoma-specific versions) [18]; the Baylor Continence Scale (BCS) [16], evaluating the social and functional impact of continence issues; the PedsQL General Well-being Scale [36]; the PedsQL Family Impact Module [36]; the Parent Experience of Child Illness (PECI) [37]; and, for those in bowel management programmes, the Patient-Reported Experience and Outcome Measures in Bowel Management Programmes (PREOM-BMP) [38]. Both French and English validated versions are available and will be used according to family language preference. Proxy-report by the parent or caregiver will be used for children aged 6–11 years; self-report will be used from age 12 onward, consistent with the validated age thresholds for each version.

**Table 3 pone.0356813.t003:** Summary of patient-reported outcome surveys.

Domain	Scale	Duration	Respondent	Brief description
Disease-specific	HAQL and BFS	10–20 min	Child (older) or Parent	Multiple-choice questions about symptoms and QoL; age-specific versions; stoma-specific items.
Social impact	BCS	10–15 min	Child (older) or Parent	23 questions on social continence and impact on life; self- or proxy-report.
General well-being	PedsQL General Well-being	4–10 min	Child or Parent (proxy)	Flexible item banks and short forms assessing physical, mental, and social health; domains include pain, fatigue, physical function, depression, anxiety, and social function.
Family functioning	PedsQL FIM	10–15 min	Parent	36-item parent-report scale assessing physical, emotional, social, and cognitive functioning, communication, worry, daily activities, and family relationships.
Parental well-being	PECI	10–15 min	Parent	25-item measure of adjustment to caring for a child with chronic illness; covers guilt/worry, unresolved sorrow/anger, long-term uncertainty, and emotional resources.
Family experience	PREOM-BMP	10–15 min	Parent	33-item survey for families of children in bowel management programmes; covers physical/emotional health, QoL, treatment success, financial considerations, schooling, and social concerns.

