*BCS, Baylor Continence Scale; FIM, Family Impact Module; HAQL, Hirschsprung's and Anorectal Malformation Quality of Life; PECI, Parent Experience of Child Illness; PREOM-BMP, Patient-Reported Experience and Outcome Measures in Bowel Management Programmes; QoL, quality of life.*

For the purposes of this registry, a bowel management programme is defined as a structured, clinician-supervised regimen of enemas, laxatives, or dietary modification,  prescribed and monitored by the COCOE team,  for the management of fecal incontinence or constipation that has not responded to first-line measures. Eligibility for the PREOM-BMP is determined at each clinic visit by the responsible clinician and recorded in REDCap. Based on current COCOE caseload, approximately 40–50% of enrolled participants are expected to be in a formal bowel management programme at any given assessment visit.

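### The ARM primary event does not separate unaided continence from cleanliness under bowel management, so the planned comparison with published full-continence rates is not shown to be like-for-like

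*Protocol article*

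**What the plan says.** Under Outcome measures, the primary outcome is time from definitive repair to faecal continence. For ARM the instrument is the Baylor Continence Scale (BCS), "with social continence defined as no soiling episodes in the preceding 4 weeks per published BCS criteria". For HD the event is a Bowel Function Score (BFS) of at least 17. Table 2 adds confirmation at a later visit: "First clinic visit (confirmed at subsequent visit) at which the participant meets social continence threshold: BCS criteria (ARM) or BFS ≥ 17 (HD"). Neither the table nor the text says whether a child who is clean on a bowel management regimen has had the event. The same section starts assessment at age 3 as "consistent with normal developmental milestones for voluntary bowel control".

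Under Patient-reported outcomes, below Table 3, a bowel management programme is "a structured, clinician-supervised regimen of enemas, laxatives, or dietary modification", used for incontinence or constipation that first-line measures have not resolved. There, "approximately 40–50% of enrolled participants are expected to be in a formal bowel management programme at any given assessment visit". Eligibility for the programme questionnaire (PREOM-BMP) is recorded in REDCap at each visit; selecting who receives that questionnaire is its only stated use.

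The Introduction reports that "only 24% of patients with ARM achieved full bowel control across over 500 patients". The sample size section cites the same study for an ARM rate of about 24–30% with full continence, and uses it in the event projection. Statistical analysis, Objective 3, plans the proportions continent by ages 5 and 10 "to allow benchmarking against published ARM and HD cohort data".

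**The concern.** The ARM event measures freedom from soiling by any means. The figures used to project it, and the only ARM figures the article offers for comparison, are described as full continence or full bowel control. In a registry where up to half of participants may be on a regimen intended to manage incontinence or constipation, the two can differ materially.

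Three outputs are affected. The ARM Kaplan–Meier curve would combine children who gained control with children kept clean by treatment. The landmark proportions could compare favourably with published cohorts for that reason alone. The ARM Cox model could pass its threshold of 10 events per variable with events of a different kind from those projected. Programme status appears in none of the places that would separate the two: the event definition, the ARM Cox predictors (Krickenbeck category, age at repair, sex, syndromic status, deprivation) or the competing risks (death and transition).

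**Working it through.** **1. The plan's own projection.** Events = enrolment × event rate. 480 × 0.30 = 144 and 680 × 0.35 = 238, against the stated 145–240. Dividing by 10 gives 14.4 and 23.8, against the stated 14–24 covariates. The arithmetic reproduces. It is for HD and ARM combined, and its ARM component is a full-continence rate applied to a no-soiling event.

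**2. The definitions side by side.**
- ARM event: no soiling in 4 weeks, confirmed at a later visit; no condition on treatment.
- ARM projection: full faecal continence, 24–30%.
- ARM figure in the Introduction: full bowel control, 24%.
- HD event and HD projection: both BFS of at least 17 (39% by adolescence). These match.

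Confirmation at a later visit does not separate the two kinds of ARM event, because a child kept clean by a regimen can be clean at both visits.

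**3. Illustration of size.** Let
- T = proportion with unaided control, 0.24–0.30 (protocol's cited rate, read as unaided);
- p = programme share among children without control, 0.40–0.50 (assumption: the protocol gives this share for all participants, both diseases);
- c = share of those programme children with no soiling in 4 weeks, 0.20–0.60 (assumption: not in the document).

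Apparent proportion = T + (1 − T) × p × c, so the excess is (1 − T) × p × c.

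| T | p | c | Excess | Apparent | Managed share of events |
|---|---|---|---|---|---|
| 0.30 | 0.40 | 0.20 | 0.70 × 0.40 × 0.20 = 0.056 | 0.356 | 0.056/0.356 = 16% |
| 0.24 | 0.40 | 0.20 | 0.76 × 0.40 × 0.20 = 0.061 | 0.301 | 0.061/0.301 = 20% |
| 0.30 | 0.50 | 0.60 | 0.70 × 0.50 × 0.60 = 0.210 | 0.510 | 0.210/0.510 = 41% |
| 0.24 | 0.50 | 0.60 | 0.76 × 0.50 × 0.60 = 0.228 | 0.468 | 0.228/0.468 = 49% |

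The excess runs from 5.6 to 22.8 points, and the apparent proportion from 30% to 51%. At c = 0 there is no excess.

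**4. How the assumptions push the result.** If programme children were all children without control, the excess would be p × c: 0.40 × 0.20 = 8 points to 0.50 × 0.60 = 30 points. In the other direction, the 40–50% includes laxatives and diet, so it is an upper bound on enema use. It is also not an ARM figure, and the ARM share could be higher or lower.

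**The case against.** The strongest reply is that the threshold is named social continence, and that freedom from soiling by any means is a coherent, patient-centred endpoint. The reference to voluntary control justifies the starting age; it does not define the event. This stands, and it is a reason to split the event rather than replace it. It does not settle the comparison: if managed cleanliness is meant to count, the projection and benchmark need rates defined the same way.

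A second reply is that the mismatch is inferred from labels. The cited cohorts and the published BCS criteria are not available here, and the comparators may themselves have admitted children on laxatives or enemas. This also stands. The supportable statement is that equivalence has not been shown, not that benchmarking is impossible.

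A reader might infer four stronger points that the document does not support:
- **Later unaided continence is lost.** It is not. The child leaves the risk set for the first event, but both instruments continue at annual visits and collection runs to age 18.
- **A child with a stoma trivially meets the event.** Nothing excludes such a child, and the quality-of-life instrument (HAQL) covers "disease-specific symptoms and quality of life, with age-specific and stoma-specific versions". But the clock starts at definitive repair, and neither the number with a stoma afterwards nor how the BCS is scored with one is given.
- **The Krickenbeck severity effect would reverse.** No figure gives programme use or cleanliness by category.
- **HD has the same fault.** Its stated comparator uses the same BFS threshold, and nothing shows that a child on enemas reaches it.

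**Conclusion.** The point holds for ARM. The event is fully stated in the protocol article and, followed as written, admits managed cleanliness, while the projection and the cited ARM rates are described as full continence or full bowel control. The ARM landmark comparison is therefore not shown to be like-for-like and may be inflated. The amount cannot be derived, because the document gives neither the ARM programme share, the mix of regimens, nor the proportion clean on a programme. The 5.6–22.8 points depend on an assumed 20–60% clean, on applying the all-participant programme share to ARM children without control, and on reading 24–30% as unaided. They show what is possible and are not an estimate of bias. Because this is the primary outcome and the article states that no formal analysis has yet been done, it should be settled before the first interim analysis planned for Year 3.

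**What to change.** In the primary outcome text and Table 2, state that each ARM continence event is classified, at the event visit, as unaided or achieved under bowel management. Use the programme status already recorded in REDCap at each visit, and add a regimen-type field and a stoma field. State which recorded regimens fall in which class, so that the split can be matched to a comparator.

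Then:
- report the ARM Kaplan–Meier curve and the age-5 and age-10 proportions for both classes;
- for the unaided curve, keep a child who is clean only under management in follow-up, since the annual assessments continue;
- benchmark on the unaided proportion, or on the comparator's own definition where that is known;
- count the ARM events-per-variable trigger on the event type actually modelled, and say which ARM event the 24–30% projection refers to.

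Leave the HD event at BFS of at least 17.

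The cost is protocol wording and one or two extra fields. Unaided events will be fewer, so the adjusted ARM model may be triggered later. Early action matters because the protocol records programme eligibility but not, as far as it states, regimen type at each visit, which may be hard to recover afterwards. Nothing in this changes care.
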